**Methods/design:**

This randomised multi-centre, single-blinded clinical trial is intended to compare IMR with treatment as usual for 200 outpatient clients with a severe and persistent mental illness (SMI). We will investigate whether IMR leads to better illness management, fewer symptoms and fewer relapses, and also to better subjective and objective recovery. The primary outcome measure is the score on the client version of the Illness Management and Recovery Scale. Secondary outcome measures are the clinician version of the Illness Management and Recovery scale, measures of illness management, coping, symptoms, the number of relapses, and measures of recovery. Measurement will take place before randomisation, and 12 and 18 months after randomisation.

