### Hypotheses

We have two primary hypotheses and four secondary hypotheses. The first primary hypothesis is that IMR + CAU (IMR offered in group format) leads to better illness management and to fewer symptoms and relapses than CAU only. The second primary hypothesis is that IMR + CAU leads to better ‘subjective’ and ‘objective’ recovery than CAU only. We thus expect a condition x time interaction effect of the IMR + CAU group over the CAU-only group.

The first secondary hypothesis is that the cost-utility of IMR + CAU is better than that of CAU.

We intend to explore the working mechanisms of IMR by testing the second secondary hypothesis that better illness management (i.e. getting greater psychiatric insight, better coping, more social support, less addiction and better service engagement) leads to fewer symptoms and relapses. We also intend to test the third secondary hypothesis that better ‘distal outcomes’ (i.e. recovery, see Fig. 1) result from a combination of better ‘proximal outcomes’ (i.e. better illness management and fewer symptoms and relapses) and progress on personal goals [2]. Finally, we expect that any improvement resulting from IMR + CAU will be associated with the fidelity of IMR implementation (fourth secondary hypothesis).

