#### Illness management and illness outcomes

The primary outcome measure is the self-rated IMRS [23, 24] with 15 items completed by clients themselves. One of the secondary outcome measures is the clinician-rated IMRS [23, 24]. The IMR scales have good validity and moderate reliability [25, 26]. To identify and correct discrepancies, the Dutch translation has been independently back-translated into English and compared with the original version. Evidence has been provided for the reliability and validity of this Dutch version [27].

These two IMR scales are not unidimensional measures [25, 28]. Three factors were found: ‘Coping with Illness Outcome’, ‘Knowledge and Goals’, and ‘Effective Medication Use/Reduced Alcohol and Drug Abuse’ [25]. In terms of Mueser’s framework, the items of these two IMR scales mainly concern aspects of illness management and illness outcomes.

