#### Recovery

In Mueser’s conceptual framework [2], the concept of recovery is differentiated into subjective recovery and objective recovery. The concept of subjective recovery is complex. Mueser divides subjective recovery into perceived recovery, sense of purpose and personal agency, and divides objective recovery into social and role functioning. As secondary outcome measures we will use five scales to assess subjective recovery and one longer scale for objective recovery.

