### Statistical analysis

The analyses will be based on the intention-to-treat principle. Generalized linear mixed models will be used to investigate group difference between the experimental and control conditions [52, 53], with times of measurement nested within study participants. As well as the main effects of time and condition, we will investigate whether there is a time x condition interaction effect with respect to symptoms, health complaints, number of relapses and recovery. Because number of relapses is a count variable, the analysis will use a mixed model for the poisson or negative binomial distribution. We will also test whether the addition of a random effect for the time variable results in a better model fit in each of the analyses. For the recovery outcome, we will investigate the influence of illness management, symptoms, relapses and progress on personal goals, as well as their interaction with time. Akaike’s Information Criterion (AIC [54]) will be used for statistical model selection in these analyses.

To explore associations between illness-management outcomes and recovery outcomes, we will use structural equation modelling. To investigate the associations between improvement of symptoms, recovery and fidelity (within IMR + CAU), linear mixed models will be used, with clients nested within IMR groups. As well as a fixed effect for the trainer’s fidelity score, a random intercept at the group level will be incorporated. Before testing the first and second primary hypotheses, we will test the fourth secondary hypothesis: ‘we expect that any improvement resulting from IMR + CAU will be associated with the fidelity with which IMR is implemented.’ If fidelity has an effect, it will be included as a covariate in the subsequent analyses.

Clients will be classified as completers of the study if they have finished all three interviews. After the intention-to-treat analyses, we will perform secondary analyses to measure the effects in clients who have completed IMR.

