### Limitations

Firstly, no structured diagnostic interview will be used to confirm the DSM-IV diagnosis. Practical considerations underlay our choice of the clinical diagnosis reported by clinicians on the basis of the medical records; due to the limited relevance of a DSM-IV diagnosis to the present study, this seems to be sufficient.

Another limitation is the chance of recruitment bias. As we consider clinicians to be responsible for treatment, it will be they who suggest that particular clients participate in IMR, and who inform these clients about the study. Although an interview with an assistant researcher will be used to screen all clinicians’ total caseloads for their potential suitability for IMR, and although the clinicians are indeed supposed to ask all selected clients to participate in IMR and to inform them about the study, some clinicians may prefer certain clients for participation in IMR—those whose functioning is better, for example. Some of these selected clients are therefore likely to participate in this study. We will explore which criteria the clinicians use to select participants for IMR.

A further limitation is that the clinicians who score two questionnaires will not be blind for the condition. On the other hand, they will not be involved in the IMR training. Neither, due to the use of self-score questionnaires, will they be blind for the clients.

The use of multiple scales to assess aspects of objective and subjective recovery is a limitation, as multiple testing may introduce positive findings. However, given the comprehensive nature of the IMR model and training programme, we felt that it would not be enough to use IMR scales alone [23, 24], and that a more comprehensive set of scales was needed.

By limiting the cost-utility analyses to health care consumption alone, we will not be able to include potential reductions in social costs, such as those that might occur if IMR participants manage their symptoms well enough to be able to work. But a full assessment of costs is beyond the scope of this study.

Finally, IMR will be offered in our study in a group format, and will be compared with care as usual, which will largely involve an individual format. Some of the possible effect in a group format may be attributable to peer-group support.

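### The recovery hypothesis is called primary but rests only on secondary, unpowered scales, and the listed interaction tests leave out the one declared primary outcome, the client IMRS

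*Protocol article*

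**What the plan says.** **Primary outcome.** The Abstract (Methods/design) states: "The primary outcome measure is the score on the client version of the Illness Management and Recovery Scale". The section Illness management and illness outcomes repeats it: "The primary outcome measure is the self-rated IMRS". Sample size ties the effect size of 0.40, alpha of 0.05 and power of 0.80 to this scale and to no other. The protocol describes the IMRS items as ones that "mainly concern aspects of illness management and illness outcomes".

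**Primary hypotheses.** The Hypotheses section says: "We have two primary hypotheses and four secondary hypotheses". The first primary hypothesis is that IMR plus care as usual "leads to better illness management and to fewer symptoms and relapses than CAU only". The second is that it gives better subjective and objective recovery. A condition x time interaction is expected for both. The Discussion repeats both hypotheses.

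**Status of the other measures.** The additional illness-management scales are labelled secondary, as are symptoms, health complaints and relapses. On recovery the protocol says: "As secondary outcome measures we will use five scales to assess subjective recovery and one longer scale for objective recovery". The Subjective recovery section then describes progress on personal goals, measured by the goals template, as a mediator between illness self-management and recovery.

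**Listed tests.** In Statistical analysis, "we will investigate whether there is a time x condition interaction effect with respect to symptoms, health complaints, number of relapses and recovery". The same section later refers to testing the first and second primary hypotheses. Limitations concedes, for the recovery scales, that "multiple testing may introduce positive findings".

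**The concern.** The trial has two hierarchies that do not agree. By outcome, the client IMRS is primary and everything else is secondary. By hypothesis, recovery, symptoms and relapses are primary too. The analysis section follows the second hierarchy and does not name the outcome on which the trial was sized.

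This matters when the results split, which the protocol's own Table 1 shows can happen. In the earlier 41-participant trial the client IMRS was significant (.29) and recovery was not. If this trial repeats that pattern, its primary outcome is met and one of its primary hypotheses fails. The reverse pattern would let a primary hypothesis be reported as confirmed on scales that were never powered and are called secondary elsewhere. No recovery scale is named to decide the matter.

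**Working it through.** **Step 1. Set the labels side by side.**

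| Domain | Status as hypothesis | Status as outcome | In the listed time x condition tests? |
|---|---|---|---|
| Client IMRS (illness management and illness outcomes) | Primary 1, in large part | Primary, powered | No |
| Other illness-management scales | Primary 1 | Secondary | No |
| Symptoms, relapses | Primary 1 | Secondary | Yes |
| Health complaints (EQ-5D) | Not named in either | Secondary | Yes |
| Subjective and objective recovery | Primary 2 | Secondary | Yes |

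The IMRS largely fits hypothesis 1 and does not address hypothesis 2. Everything named in the test list is secondary as an outcome.

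**Step 2. Count the instruments (Table 2 and the instrument sections).**
- Recovery: Mental Health Recovery Measure, internal stigma scale, self-esteem scale, satisfaction item and goals template make the five subjective scales. The Social Functioning Scale makes six. Without the goals template (the mediator) there are five.
- Listed tests: one symptom scale, the EQ-5D, relapses counted once, and five or six recovery scales, so k = 8 or 9.
- All repeated outcomes in Table 2: k = 16.

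**Step 3. Illustrate the error rate.** Assumptions, none of them stated in the protocol for these scales: each tested two-sided at 0.05, independent, no true effects, and any one significant scale counts as success. Then P(at least one) = 1 − 0.95^k. Counting only results in favour of IMR, it is 1 − 0.975^k.

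| Set | k | Two-sided | Favouring IMR only |
|---|---|---|---|
| One test per primary hypothesis | 2 | 0.098 | 0.05 |
| Recovery without goals template | 5 | 1 − 0.774 = 0.23 | 1 − 0.881 = 0.12 |
| Recovery, all six | 6 | 1 − 0.735 = 0.26 | 1 − 0.859 = 0.14 |
| Listed tests | 8 | 0.34 | 0.18 |
| Listed tests | 9 | 0.37 | 0.20 |
| All of Table 2 | 16 | 0.56 | 0.33 |

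Simulating equally correlated z statistics (400,000 draws) lowers the two-sided figures. For k = 8 and 9 they are 0.30 and 0.33 at correlation 0.3, 0.25 and 0.27 at 0.5, and 0.19 and 0.20 at 0.7.

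**Step 4. The stated sample size.** A single-time two-sided comparison at d = 0.40 needs 99 per arm, 198 in total. The stated 148 is reached with an assumed correlation of 0.5 (baseline-adjusted analysis, or mean of two follow-ups). The correlation is not given, so 148 is plausible but cannot be confirmed. It is not an error and does not bear on this point, except that it belongs to the IMRS alone.

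**The case against.** The strongest reply is that the primary outcome is not in doubt. It is named in the Abstract and the instruments section and is the only outcome in the power calculation. The other measures are consistently called secondary. On that hierarchy a positive IMRS with null recovery is a trial that met its primary outcome. Nor is the IMRS without a test: Hypotheses expects a condition x time effect for both primary hypotheses, Sample size assumes a mixed model with three measurements, and Statistical analysis opens with mixed models for group differences in general. The missing name may be a drafting slip in a condensed article. All of this stands, and it limits the point. It does not remove the second primary hypothesis or say which scale decides it.

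A reader might go further and infer that primary success can be claimed on any of 16 outcomes, each at 0.05, with a 56% false-positive risk. The document does not support that. Alpha of 0.05 appears only in the IMRS sample-size calculation, and no any-outcome success rule is stated. The first hypothesis joins its parts with *and*, which can equally be read as a joint claim. The count of 16 includes the IMRS itself, a mediator, and a health-complaints scale named in neither hypothesis.

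Multiplicity control for secondary scales may also sit in an analysis plan that is not shown, so its absence is not raised here. An analysis plan could not, however, make these sections of the protocol agree.

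**Conclusion.** The inconsistency is in the text and holds. The mismatch is complete for the second primary hypothesis, which rests entirely on secondary scales. It is partial for the first, where the IMRS covers much of the domain but symptoms and relapses are secondary. The list of interaction tests omits both the IMRS and illness management.

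The size is illustrative: about 23–26% for the recovery hypothesis and 34–37% for the listed tests, under independence, 0.05 per test and any-scale success. Correlation, or counting only results favouring IMR, brings these down. The 56% for all of Table 2 is an upper bound resting on a rule the protocol does not state. It should not be read as the trial's error rate. What does not depend on these assumptions is that no endpoint is named to decide the recovery hypothesis.

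**What to change.** 1. In Statistical analysis, state that the confirmatory test is the condition x time effect on the client IMRS total at alpha 0.05, and add the IMRS to the list of interaction tests.
2. Relabel the recovery hypothesis, and the symptom and relapse part of the first hypothesis, as secondary, in both Hypotheses and Discussion.
3. If recovery is to stay primary, name one recovery scale and test it only after a significant IMRS result, or split alpha between the two.
4. State whether the goals template is a recovery outcome or a mediator.

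The change is wording only and needs no extra participants. It should be made before results by arm are seen, so that the choice cannot follow the data. The price is fewer confirmatory claims. Testing in sequence costs the IMRS no power. Splitting alpha to 0.025 each lowers IMRS power from about 0.89 to 0.83 at 120:80, taking the variance implied by 74 per arm and assuming complete follow-up.

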### Sample size

On the basis of the effect sizes of the studies by Hasson-Ohayon et al. (2007), Levitt et al. (2009) and Färdig et al. (2011) [16–18], we anticipate a medium effect size of 0.40 on the primary outcome variable (self-rated IMR scale, Mueser et al. 2004, 2005 [23, 24]). On the basis of the power analyses with three times of measurement (mixed models), equal allocation to the experimental and control groups, a power of .80, alpha at 0.05, and an effect size of .40, it will be necessary to randomize 148 clients: 74 to the experimental condition and 74 to the CAU group [50, 51].

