### Randomisation

Because IMR is a relatively long-term care programme—in our pilot study at least 8 months at one session per week—the drop-out from treatment may be relatively high. Other studies had 29 % [17], 15 % [18]; 51 % [20], and 72 % [15]. Due to the 50 % drop-out rate expected from treatment in the experimental condition (a pessimistic estimate), we have chosen to allocate more clients to the experimental condition (IMR) than to the CAU group (proportions of 3:2). We will randomise 200 clients (on the basis of a conservative calculation): 120 to the experimental condition and 80 to the CAU group.

Randomisation will be stratified by team. To ensure the right distribution of clients per team in the two groups, envelopes containing five lots per team will be used each time. For this we will use a randomisation plan from http://www.randomization.com. After completing the baseline interviews, the principal investigator will allocate participants to the experimental group or control group.

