### Strengths

The first strength is that our use of different outcome measures for each domain will provide a thorough measurement of the effects of IMR on illness management and on subjective and objective recovery. And as well as exploring the contribution made by various illness-management variables to illness outcomes, we will also explore the contribution that progress on personal goals makes to subjective and objective recovery. In this way we will be able to analyse the working mechanisms of Mueser’s conceptual framework [2].

Other strengths of our study are that it will be conducted in another country than the earlier RCTs. By including 200 participants with various types of SMI, it will also have a relatively large sample size. The numbers of participants in the other completed RCTs were 210 [17], 104 [18], 41 [16] and 118 [15]. As the study will be conducted in the everyday clinical practice of the two participating mental health institutions, the generalisability of its results will be good. The measurement procedure at the second and third time of measurement will be single blinded.

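### The recovery model does not separate within-client from between-client association, so its main terms and AIC choice cannot by themselves support the third secondary hypothesis

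*Protocol article*

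**What the plan says.** The Statistical analysis section specifies generalized linear mixed models "with times of measurement nested within study participants". For the mechanism question it continues: "For the recovery outcome, we will investigate the influence of illness management, symptoms, relapses and progress on personal goals". The same sentence adds the interactions of these variables with time, and AIC is named for model selection. A structural equation model is also planned, to explore associations between illness-management and recovery outcomes. The article does not say whether the predictors enter as measured, centred, lagged or as change scores.

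The Hypotheses section places this under exploring how IMR works, but uses the language of testing. It speaks of "testing the second secondary hypothesis that better illness management" leading to fewer symptoms and relapses. It then says that a third secondary hypothesis will also be tested: better recovery results from better illness management, fewer symptoms and relapses, and progress on goals. The Discussion repeats both. The Strengths section says "we will also explore the contribution that progress on personal goals makes to subjective and objective recovery" and concludes that the working mechanisms of the framework can be analysed in this way.

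**The concern.** The third secondary hypothesis concerns change: clients whose illness management and symptoms improve should be those whose recovery improves. In a random-intercept model with a time-varying predictor entered as measured, one coefficient blends two associations. One is between clients (those who generally cope better generally feel more recovered). The other is within clients (when a client's coping rises, so does that client's recovery). Only the second bears on the hypothesis.

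Table 2 shows why the first is likely to be present. CSES, MSPSS, the Insight Scale, the ASI item, the client IMRS and the BSI are reported by the client. So are MHRM, ISMI, SERS-SF, the satisfaction item and the Social Functioning Scale. General severity or response style can link such scores before randomisation, whatever IMR does. At stake is whether a significant or AIC-preferred predictor could be taken as evidence for the mechanism when it reflects only who the clients are.

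**Working it through.** **The plan's own figure.** The mechanism analysis has none. The only stated figure is for the primary outcome: "a power of .80, alpha at 0.05, and an effect size of .40", giving 148 clients. Two-sided, 2 × (1.96 + 0.8416)² / 0.40² = 98.11 per arm. With baseline adjustment at an assumed correlation of 0.5, 98.11 × (1 − 0.5²) = 73.6, so 74 per arm and 148 in all. It is reproducible and not at issue here.

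**Inputs from the article.** 200 clients (120 and 80), three measurements, a mixed model with visits within clients, predictor and predictor × time terms, AIC.

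**Assumed inputs (not in the article).** Intraclass correlation (ICC) 0.4 to 0.7, the same for predictor and outcome; between-client correlation r of 0, 0.3, 0.5 or 0.7; within-client correlation exactly 0; no treatment effect; complete data; one predictor at a time.

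**One case by hand (ICC 0.6, r = 0.5, unit variances).**

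- Between-client slope: 0.5 × 0.6 / (0.6 + 0.4/3) = 0.30 / 0.7333 = 0.409. Within-client slope: 0.
- Residual variances at the fitted coefficient b = 0.148: within, 0.4 × (1 + 0.148²) = 0.4088; between, 3 × (0.7333 − 2 × 0.148 × 0.30 + 0.148² × 0.7333) = 1.982.
- Information per client: within, 2 × 0.4 / 0.4088 = 1.957; between, 3 × 0.7333 / 1.982 = 1.110.
- Pooled coefficient: 0.409 × 1.110 / (1.957 + 1.110) = 0.148, which agrees with the value assumed.
- Standard error: 1 / √(200 × 3.067) = 0.0404, so z = 0.148 / 0.0404 ≈ 3.7 and rejection is expected in about 96% of trials.

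The simulation gave a mean coefficient of 0.148 and 94% rejection, so the two agree.

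**Simulation.** 600 trials per row, maximum-likelihood random-intercept model with categorical time, condition and their interaction, N = 200:

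| ICC | r | Raw term significant | AIC keeps raw term | Raw term significant, predictor × time also in model | Within-client term significant |
|---|---|---|---|---|---|
| 0.4 | 0 | 4.5% | 14.7% | 4.3% | 4.7% |
| 0.4 | 0.3 | 37.5% | 57.0% | 18.7% | 4.2% |
| 0.4 | 0.5 | 82.2% | 91.8% | 46.0% | 4.8% |
| 0.4 | 0.7 | 98.7% | 99.3% | 83.0% | 4.0% |
| 0.6 | 0.3 | 53.0% | 72.2% | 33.7% | 5.5% |
| 0.6 | 0.5 | 94.3% | 97.8% | 77.5% | 6.0% |
| 0.6 | 0.7 | 99.7% | 99.8% | 98.2% | 4.5% |
| 0.7 | 0.3 | 59.7% | 75.8% | 42.8% | 5.5% |
| 0.7 | 0.5 | 97.0% | 99.0% | 85.3% | 4.2% |
| 0.7 | 0.7 | 100% | 100% | 99.8% | 5.0% |

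With 140 clients, an assumption to allow for loss, the raw term is significant in 29% to 100% of trials for r of 0.3 to 0.7.

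**The time interactions.** The predictor × time term was significant in 4% to 7% of trials in every setting, so stable differences do not inflate it. But it asks whether the slope of recovery on the predictor differs between visits, not whether a client's changes go together. With a real within-client correlation of 0.3, it was significant in only about 5% of trials, against 100% for the within-client term.

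**The case against.** The strongest reply is that entry as measured is inferred. The article does not fix the coding, a fuller plan may do so, and an article may leave such detail out. That is right, and a reader who inferred that the plan prescribes raw scores would go beyond the text. What remains is that the article does name the model, the predictors, the interactions and the selection rule, and says the hypothesis will be tested. It mentions no separation, although in the fidelity analysis it speaks of improvement where it means change.

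Four further points stand in part.

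- The article adds time interactions, and these are not inflated. They do not test the hypothesis either.
- The shared self-report argument does not cover every predictor. Admissions come from records, and SES and the clinician IMRS are rated by clinicians, so it has less force there. Goal progress is already a progress measure, rated by research assistants through the clinician, and is hardly touched.
- The SEM is a second route and could model change. The article describes it only as exploring associations.
- The rates depend on the assumed ICC and correlation and on one predictor at a time. Mutual adjustment among several would change them.

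A reader might also infer that the analysis says nothing about mechanism, or that the trial will report a false mechanism. Neither is supported: the pooled coefficient contains some within-client information, and the article commits to no such conclusion. It describes the work partly as exploratory.

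**Conclusion.** The concern holds in a limited form. As described, the recovery model does not isolate the within-client association that the third secondary hypothesis is about. If the scores enter as measured, the main terms and the AIC choice can favour that hypothesis because of stable client differences alone. At N = 200 this happens in about 38% to 100% of null trials by significance and 57% to 100% by AIC, over the assumed ICC of 0.4 to 0.7 and between-client correlation of 0.3 to 0.7. With the time interaction included, the main term is still significant in 19% to 100%. With no between-client correlation there is no inflation. The finding is confined to a secondary, partly exploratory analysis, and mainly to the self-reported illness-management scales and the BSI. The primary outcome, the randomised comparison and the sample size are untouched.

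**What to change.** In the Statistical analysis section, state that each time-varying illness-management and symptom predictor enters the recovery model as two terms: the client's mean over visits and the visit's deviation from that mean. Keep time, condition and time × condition in the model. Base the third secondary hypothesis on the deviation term, and report the client-mean term as descriptive. Give the SEM an equivalent structure, by change scores or random intercepts. Add that a within-client association is necessary but not sufficient for a causal mechanism, because same-visit mood or reverse influence can also produce it.

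This needs a sentence or two and a recoding of data already planned. The price is precision. With complete data and equal ICCs, and with no association present, the within-client term uses 2 of 3 units of information per client. Its standard error is then 1/√(200 × 2) = 0.050 against 1/√(200 × 3) = 0.041 for the pooled term, so its interval is about √(3/2) = 1.22 times as wide.

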## Design

This research project entails a randomised controlled trial in which clients who provide written informed consent will be assigned to the experimental condition (IMR) or the control group. The experimental group will consist of clients who participate in the IMR programme (which will be offered in a group format) and also get CAU. The control group will receive CAU.

Measurement is planned to take place before randomisation and at 12 and 18 months after randomisation.

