### IMR model fidelity

To promote the fidelity of the intervention, the trainers will be experienced clinicians (mostly psychiatric nurses) who will receive a 2-day course in teaching IMR before the study starts and who will attend supervision once every 2 weeks for 2 h. Twice a year, all IMR trainers will come together for a morning or afternoon of additional training.

To measure whether the IMR-programme is implemented according to the original intent, the researchers will determine model fidelity using the IMR fidelity scale and the IMR General Organisational Index (GOI) [19, 21]. These scales have been translated, and the principal investigator was trained in their use by two American specialists ([name], Ph.D. and A. [name], both of UIPUI, University of Indianapolis USA). We will also use the Illness Management and Recovery Treatment Integrity Scale (IT-IS) [22], which gives more precise information on the quality of the trainers’ interventions. These fidelity scales will be applied by the principal researcher and a research assistant, scoring independently according to a protocol. For one team, fidelity measurement takes almost a day, and consists of interviews with two participants and the two trainers, in addition to observation of one session, and checking forms. The researchers will give periodic feedback in the supervision groups on the results of the fidelity measurements.

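### IMR fidelity, measured after randomisation and only on IMR delivery, should not be pre-tested and then entered as a covariate in the IMR-versus-CAU comparisons

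*Protocol article*

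**What the plan says.** The Statistical analysis section sets the order of testing: "Before testing the first and second primary hypotheses, we will test the fourth secondary hypothesis". That hypothesis links improvement to fidelity of implementation. The rule follows directly: "If fidelity has an effect, it will be included as a covariate in the subsequent analyses". Given the stated order, the later analyses include the tests of both primary hypotheses, which the Hypotheses section frames as a condition x time interaction between IMR + CAU and CAU only. The same section commits the analyses to intention to treat.

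The article also says what fidelity is:

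- **Level.** The fidelity model concerns "improvement of symptoms, recovery and fidelity (within IMR + CAU), linear mixed models will be used, with clients nested within IMR groups", and its predictor is "a fixed effect for the trainer’s fidelity score". IMR + CAU is the article's name for the experimental arm.
- **Source.** Under IMR model fidelity, the assessment of one team "consists of interviews with two participants and the two trainers, in addition to observation of one session, and checking forms".
- **Timing.** Table 2 places it between M1 and M2. The Design section states: "Measurement is planned to take place before randomisation and at 12 and 18 months after randomisation". M1 is therefore the pre-randomisation visit, and the delivery being scored comes after it.
- **Controls.** "The control group will receive CAU". They have no IMR trainer or IMR session to be scored. The article gives them no fidelity value and no coding.

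**The concern.** A covariate in a randomised comparison should be fixed before treatment starts and have a meaning in both arms. Fidelity fails on both counts: it describes how well the experimental treatment was delivered. Entered beside the condition indicator, it can change what the condition coefficient means, from the average effect of being allocated to IMR to the effect at whatever fidelity value the controls happen to be given.

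The trigger is a second problem. Whether the primary model contains fidelity is decided by a test on outcome data in one arm, carried out before the primary test. The headline estimate could then rest on a coding choice that the article does not make, applied after outcomes have been examined. That sits badly with the stated intention-to-treat principle.

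**Working it through.** **Inputs from the article.** 120 IMR and 80 CAU clients (Randomisation); effect size 0.40, power 0.80, alpha 0.05 (Sample size); three measurements; condition x time as the tested contrast (Hypotheses).

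**Assumptions, not in the article.** Within-person correlation 0.5; 14 IMR groups; mean fidelity 4 on a 1 to 5 scale, SD 0.5 between groups; slope of outcome on fidelity 0.3 SD per point, with 0 to 0.4 as the range; two-sided tests.

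**The plan's own figure.** With no gain from repeated measures, n per arm = 2 x ((1.96 + 0.84)/0.40)^2, about 98.1. Multiplying by 1 - 0.5^2 = 0.75 gives 73.6, rounded up to 74 per arm, or 148 as stated. The match depends on the assumed correlation and does not bear on the concern. It supplies the residual variance of 0.75 used in step 2.

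**1. Fidelity missing in CAU.** A model with fidelity drops every row of the 80 controls. Among the remaining 120 clients, the condition column equals the intercept column, so the matrix of intercept, condition and fidelity has rank 2 of 3. Neither condition nor condition x time can be estimated. This needs none of the assumptions.

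**2. CAU coded as a constant c, one endpoint.** The condition coefficient becomes

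(average effect) - slope x (mean fidelity - c).

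- c = 0: 0.40 - 0.3 x 4 = -0.80
- c = 1: 0.40 - 0.3 x 3 = -0.50

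The variance without fidelity is 0.75/120 + 0.75/80 = 0.015625, so SE = 0.125. The slope has variance 0.75/(120 x 0.25) = 0.025. With c = 0 the variance is 0.015625 + 16 x 0.025 = 0.4156, so SE = 0.64. With c = 1 it is 0.015625 + 9 x 0.025 = 0.2406, so SE = 0.49. Simulation also lets the 14 group scores vary between trials. It gave -0.80 (SE 0.72) for c = 0 and -0.49 (SE 0.55) for c = 1, against 0.40 (SE 0.13) without fidelity. At slope 0 and c = 0 there is no bias, but rejection fell from about 90% to 9%.

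**3. The planned contrast, condition x time.** The simulation used three measurements and a random intercept.

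| Fidelity in the model | CAU coding | Slope | Condition x time |
|---|---|---|---|
| Time-constant main effect only | 0 or 1 | 0 or 0.3 | Unchanged: about 0.40, SE about 0.125 (follow-ups pooled) or 0.144 (M3 alone) |
| Also interacting with time | 0 | 0.3 | -0.77, SE 0.71 |
| Also interacting with time | 1 | 0.3 | -0.50, SE 0.54 |
| Also interacting with time | 0 | 0 | Power 9% instead of 89% |
| Also interacting with time | 1 | 0 | Power 13% instead of 89% |

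The first row follows from the structure of the model. With complete data, a time-constant covariate acts between persons, while condition x time is a within-person contrast. With 25% missing at each follow-up, the largest difference in any single run was 0.012.

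**4. Other codings (one endpoint).** Centring fidelity within IMR with CAU at 0, giving CAU the IMR mean, or giving a team score to both arms all left the estimate at about 0.40. At slope 0.4, power was 0.864 to 0.868, against 0.863 without fidelity.

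**5. The pre-test (one endpoint, CAU coded 0).** With no effects at all, the two-stage procedure rejected in about 9% of runs against a nominal 5%. With effect 0.40 and slope 0.4, fidelity was selected in 66% of runs, and the condition coefficient then averaged -1.59.

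**The case against.** The strongest reply is that the article plans condition x time in a mixed model, and the rule says only that fidelity becomes a covariate. Read as a main effect, it leaves the planned contrast alone whatever constant the controls receive. This stands, and it limits the point. A reader might infer that the primary result would reverse to -0.80 or lose nearly all its power. The documents do not support that as a general consequence, because those figures belong to the condition main effect, or to condition x time when fidelity also interacts with time. The article does not specify that interaction, although the fidelity hypothesis is about improvement, which makes it a natural choice.

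A reader might also infer that the rule can only do harm. That is too strong as well, since step 4 shows several harmless codings. A team-level reading has some footing: fidelity is measured team by team, it includes an organisational index, and randomisation is stratified by team, so controls belong to the same teams. Against it, the analysis section uses the trainer's score and nests clients in IMR groups.

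Finally, leaving the controls missing would be a poor implementation of a two-arm analysis, and the coding of controls could be left to an analysis plan that is not shown. That is fair as to coding. It does not rescue the rule: the article itself fixes both the pre-test and the entry of a post-randomisation variable into the comparisons that follow.

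**Conclusion.** The concern holds as a fault in a stated rule. Fidelity is measured after randomisation, reflects IMR delivery and is undefined for CAU clients. It should not enter the randomised comparison, and an outcome-based pre-test should not decide whether it does.

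The size depends on implementation. With CAU missing, the condition effect is inestimable, whatever the assumptions. With CAU coded 0 or 1, the condition main effect, and condition x time if fidelity interacts with time, moves from 0.40 to about -0.8 or -0.5, with a standard error roughly four to six times larger. Those figures rest on the assumed fidelity mean, SD and slope and on the assumed correlation. In the remaining readings the planned contrast is essentially unchanged. In none of those examined does the rule materially improve the comparison, so nothing is lost by removing it.

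**What to change.** Delete the sentence that makes fidelity a covariate in the later analyses. Reverse the order, so that both primary hypotheses are tested first in models without a fidelity term. Keep the fidelity analysis already described, within IMR + CAU with clients nested in IMR groups, as a secondary analysis reported after and apart from the primary comparison.

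The cost is two sentences in the Statistical analysis section. No new data are needed, and the sample size is unaffected.
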